### Comparison by normal approximation to chi-square test

For both co-primary endpoints: (I) At interim analysis after data of 240 subjects have accumulated using two-sided alpha = 0.02442 and (II) If needed, after data from 300 subjects have accumulated using two-sided alpha = 0.04288. Interim and final alphas determined by the O’Brien-Fleming method.

### Secondary efficacy analysis

Aganirsen arms combined versus placebo: secondary analyses will be considered exploratory. Time to development of anterior neovascularisation will be compared by *t* test or Wilcoxon rank sum test (depending on distribution), since missing data will be imputed using LOCF and there will be no censored data.

Continuous change from baseline to week 24 parameters (e.g. size of retinal nonperfusion areas) will be assessed by analysis of covariance (ANCOVA), the covariate being a subject’s baseline variable, to prevent regression towards the mean. If the model shows a lack of fit, ANCOVA will be conducted on ranked data. The number of additional laser treatments will be compared between groups by Poisson regression.

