The secondary objectives are to evaluate the efficacy of two aganirsen doses, to assess the aganirsen efficacy relative to placebo on time to, and intensity of, additional interventions, such as PRP or cryotherapy, to compare the effect of aganirsen and placebo on health outcome and quality of life (QoL) and to confirm a positive safety profile of aganirsen.

The aim of the imaging substudy is to develop an objective quantification of neovascularisation in the anterior part of the eye. For the biomarker substudy, the aim is to find possible biomarkers for iCRVO and NVG in tears and serum. The aim of the risk factor substudy is to identify potential novel risk factors for iCRVO and to evaluate if some of those parameters can be useful to differentiate patients who are at a higher risk of developing NVG.

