Additional exclusion criteria were defined for the eligibility of patients for the risk factor substudy: age 65 years or older, renal insufficiency and acute malignant or inflammatory reaction (systemic or local).

The co-primary efficacy endpoints combine a neovascularisation component: presence of anterior segment neovascularisation (NVI or NVA), NVD and/or NVE in the study eye requiring PRP rescue treatment or cryotherapy rescue treatment up to week 24 scored dichotomously (yes/no) and an IOP component: percentage change (≥20%) in IOP compared to baseline and >21 mmHg in the study eye scored ‘failure’, while otherwise ‘success’.

The secondary endpoints of the trial are the time of development of secondary NVG in the study eye up to week 24 (in case aganirsen does not totally inhibit but slows down the development of NVG); the time of development of anterior segment neovascularisation (NVI or NVA); NVD or NVE in the study eye requiring PRP or cryotherapy up to week 24; the development of changes in BCVA (ETDRS letter score) in the study eye up to week 24 (from baseline); the development of needed additional laser treatments and re-treatments in the study eye at up to week 24 including the intensity of the needed additional treatment; the development of changes in the size of retinal nonperfusion areas in the study eye up to week 24 in comparison with the baseline; the development of changes in the National Eye Institute Visual Function questionnaire 25 (NEI-VFQ-25) health questionnaire total score at week 24 in comparison with the baseline; the development of changes in the EuroQoL five dimensions questionnaire (EQ-5D) health questionnaire (validated questionnaires) score at week 24 in comparison with baseline; absolute change from baseline in central retinal thickness in the study eye, assessed by spectral domain optical coherence tomography (SD-OCT) at week 24; NVG classification at 24 weeks on a scale from 1 (non-NVG) to 6 (most advanced NVG) based on central reading of neovascularisation and incidence, causality and intensity of adverse events between the treatment arms.

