All randomised subjects, regardless of treatment group, may receive rescue treatment (e.g. PRP, cryotherapy or other, as routinely performed at the clinical site) at any time during the trial if they progress to anterior segment neovascularisation (NVI or NVA), NVD, or clinically relevant NVE in the fundus. In this case, the primary endpoint is reached and the patient will not further receive study medication. Should a patient receive rescue treatment with intravitreal anti-VEGF (i.e. Lucentis®, Eylea®) because of macular oedema (individual decision of the investigator), the patient will not further receive the study drug, but will be followed up for safety reasons.

The clinical trial will be performed in consideration of the Declaration of Helsinki and the International Conference on Harmonisation – Good Clinical Practice (ICH-GCP). The protocol (Version No.:1.4/Date 7 Jan 2015 Final) is approved by the institutional Ethics Committee from the Landesärztekammer Rheinland-Pfalz, Germany, and by the French Ethics Committee. Ethics approval in other participating countries/sites will follow. Any protocol amendment will be approved by the Ethics Committees and will be distributed to all participating trial sites via the sponsor’s delegated clinical research organisation. Additionally, all necessary documents in the current version will be available on a password-protected website. Personal information of participants will be treated as confidential. Only anonymous data will be forwarded to the sponsor for scientific evaluation. Data entry and storage is performed via an electronic data capture (EDC) system, including plausibility checks.

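### The stated time-to-neovascularisation analysis counts anterior vessels only, although the endpoint list, the objective, the rescue rule and the co-primary definition also cover disc and retinal vessels or intervention

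*Protocol article*

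**What the plan says.** Five places in the protocol article bear on the event.

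- **Secondary efficacy analysis:** "Time to development of anterior neovascularisation will be compared by" a t test or a Wilcoxon rank sum test, "since missing data will be imputed using LOCF and there will be no censored data". No other time analysis is described there.
- **Endpoint list** (Methods/design, printed after the exclusion criteria): "the time of development of anterior segment neovascularisation (NVI or NVA"), then a semicolon, then "NVD or NVE in the study eye requiring PRP or cryotherapy up to week 24". A separate item lists the time to secondary NVG.
- **Secondary objectives** (Background): efficacy relative to placebo "on time to, and intensity of, additional interventions, such as PRP or cryotherapy".
- **Rescue rule** (same part of Methods/design as the endpoints): patients may be rescued "if they progress to anterior segment neovascularisation (NVI or NVA), NVD, or clinically relevant NVE in the fundus". It continues: "In this case, the primary endpoint is reached and the patient will not further receive study medication".
- **Co-primary efficacy I:** the event is new vessels at any of the four sites (NVI, NVA, NVD, NVE), or rescue treatment.

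**The concern.** The event in the stated time analysis is narrower than the co-primary event and differs from the event in the objective. The gap matters because of rescue. An eye whose first new vessels are NVD or clinically relevant NVE may be rescued, has then failed the co-primary endpoint, and stops study drug. The Background describes PRP as the common therapy for neovascularisation, so anterior vessels may never appear afterwards.

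With no censoring, every eye must be given a time. If LOCF carries forward a status of no anterior vessels, a failed eye receives the same value as an eye that stayed healthy to week 24. The comparison would then partly reflect where vessels first appear and how sites use rescue, and not only whether aganirsen delays disease. It could also disagree with co-primary I for reasons of definition alone.

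**Working it through.** **1. Is there a figure to reproduce?** The article gives no power or sample size for this analysis. Its planning inputs are usable: neovascularisation by week 24 of 0.25 on aganirsen and 0.48 on placebo, 200 and 100 evaluable eyes, two-sided 0.05. The stated total is consistent with its own inputs. The IOP rates (0.41 v 0.24) at the final alpha of 0.04288, ratio 2:1, 80% power and continuity correction give 100 on placebo and 300 in all.

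**2. The event, place by place.**

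| Place | NVI/NVA | NVD/NVE | Intervention |
|---|---|---|---|
| Secondary efficacy analysis | yes | no | no |
| Endpoint list | yes | yes, if requiring PRP or cryotherapy | through that condition |
| Secondary objective | – | – | yes |
| Rescue rule | yes | yes (NVE if clinically relevant) | – |
| Co-primary efficacy I | yes | yes | yes |

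The semicolon in the endpoint list allows two readings. The NVD/NVE fragment has no lead noun, and the co-primary wording just before it joins all four sites, so one combined time endpoint is the likelier reading. If there are two endpoints, the posterior one has no analysis in this section, and the anterior one is still cut short by posterior rescue.

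**3. Eyes involved.** Expected events: 0.25 × 200 + 0.48 × 100 = 50 + 48 = 98. The article gives no anterior/posterior split, so let s be the share of first events that are NVD or NVE without later anterior vessels, and assume first that s is equal in both arms. The eyes with an event but no anterior event number 98s. The counted rates are 0.25(1−s) and 0.48(1−s), so the difference is 0.23(1−s).

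**4. Effect on power.** The simulation used exponential event times matched to 25% and 48% by week 24, gave posterior events the week-24 value, and applied the two-sided Wilcoxon test at 0.05 in 3,000 trials of 200 v 100. As a check, the two-proportion formula is power = Φ[(Δ − 1.96·SE₀)/SE₁], with SE₀ pooled and SE₁ unpooled. At s = 0.25, Δ = 0.360 − 0.1875 = 0.1725, SE₀ = 0.0527 and SE₁ = 0.0554, so power is 0.895.

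| s (assumed) | Eyes (98s) | Rates, aganirsen v placebo | Difference (points) | Wilcoxon power | Formula |
|---|---|---|---|---|---|
| 0 | 0 | 25.0% v 48.0% | 23.0 | 97.8% | 97.7% |
| 0.10 | 9.8 | 22.5% v 43.2% | 20.7 | 96.4% | 95.5% |
| 0.25 | 24.5 | 18.8% v 36.0% | 17.3 | 90.8% | 89.5% |
| 0.40 | 39.2 | 15.0% v 28.8% | 13.8 | 80.5% | 79.5% |

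A second simulation, with event times spread evenly over the week 4 to 24 visits, gave 0.97, 0.96, 0.91, 0.86 and 0.70 at s = 0, 0.10, 0.20, 0.30 and 0.50.

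**5. Unequal shares** (same second simulation).
- 10% on aganirsen and 30% on placebo: 0.25 × 0.9 = 22.5% v 0.48 × 0.7 = 33.6%, a difference of 11.1 points, power 0.53.
- 30% on aganirsen and 10% on placebo: 17.5% v 43.2%, a difference of 25.7 points, which exceeds the true 23, power above 0.99.

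**6. Would censoring at rescue be enough?** In the placebo arm at s = 0.25, 1 − KM = 1 − exp(0.75 × ln 0.52) = 0.388. The cumulative incidence is 0.75 × 0.48 = 0.36. The standard error is √(0.36 × 0.64/100) = 0.048, so the gap is 0.028, or 0.58 of a standard error. Plain censoring overstates the anterior incidence, though modestly.

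**The case against.** **The scoring is not printed.** A reader might infer that the plan states that rescued eyes are event-free to week 24. It does not. It gives only the LOCF and no-censoring rule, and both co-primary definitions count rescue as failure, so a team could apply the same here. An eye that later develops anterior vessels would also count as an event, at that later time. This stands: the scoring is the natural result of the stated rule, but it remains an inference.

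**Read literally, the analysis matches the first item in the endpoint list.** The semicolon supports this, and the article may be condensing a fuller plan. This stands in part. Analyses left to a fuller document are no fault. But the article names an event, a test and a missing-data rule, and under either reading posterior rescue cuts the anterior time short without valid handling.

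**Other endpoints address slowing of disease.** A reader might take this as the only place where slowing is examined. The endpoint list also names time to secondary NVG, expressly for the case that aganirsen delays NVG without fully preventing it. This stands.

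**The direction is not fixed.** A reader might conclude that the effect is always diluted. That holds for equal posterior shares, which no text supports. Unequal shares can push the result either way. This stands.

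**The stakes are limited.** Secondary comparisons are exploratory, with no Type I error adjustment and no power target. This stands and limits the weight of the point.

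**Conclusion.** The point holds as a mismatch in event definition, with a likely and undesirable consequence under the stated LOCF and no-censoring rule. Wilcoxon power falls from about 98% to about 96%, 91% or 80% at posterior shares of 10%, 25% or 40%.

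These figures assume that the 25% and 48% rates cover all four vessel sites, that the share is equal in both arms, that no eye with a posterior first event shows anterior vessels by week 24, and that such eyes receive the week-24 value. The documents establish none of these. The general conclusion does not need the exact figures: the result would depend on where vessels first appear and on rescue practice.

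The documents do not support a claim of bias in a known direction, or any effect on the co-primary endpoints, the sample size or alpha. The change is worth making because it is cheap. The choice of test and the premise that nothing is censored are separate questions.

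**What to change.** 1. In Secondary efficacy analysis, define the analysed event as the first of NVI, NVA, NVD or NVE requiring PRP or cryotherapy, with time to that first event. This is the endpoint list read as one combined endpoint.
2. Reconcile that wording with Co-primary efficacy I, which counts any such vessels or rescue treatment. One definition cannot match both as they now stand, so the text should say which is used and why.
3. Keep time to anterior neovascularisation as a supportive analysis. Treat rescue for NVD or NVE as a competing event and report cumulative incidence, so that time after rescue is not counted as event-free.

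**Cost:** a wording change and one further exploratory analysis. Table 1 already schedules slit lamp, gonioscopy and indirect ophthalmoscopy at every visit and assessment of rescue criteria from week 4, so no visit or examination is added. The small downside is that the main time analysis no longer isolates anterior-segment disease, which the supportive analysis retains.

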### Statistics

Presentation of the sample size is based on both aganirsen doses combined demonstrating superiority placebo on the co-primary endpoints of neovascularisation and IOP at 24 weeks. Calculation of the sample size is based on the following: (1) An aganirsen to placebo ratio of 2:1, (2) Neovascularisation measured dichotomously (NVG = yes/NVG = no) with estimated disease rates in the population of 0.25 for aganirsen and 0.48 for placebo. Testing of neovascularisation will be done using the normal approximation to the chi-square distribution for consistency with O’Brien-Fleming Alpha spending, which is also computed based on normal approximation, (3) IOP measured dichotomously with estimated rates of events in the population of 0.24 for aganirsen and 0.41 for placebo at 24 weeks and (4) Up to four performed analyses. Based on albeit heterogeneous historical data, we estimate that 25% of subjects in the aganirsen group and 48% in the placebo group will develop NVG by 24 weeks. Given a 2:1 aganirsen to placebo assignment ratio, a total of 300 evaluable subjects – 200 with aganirsen and 100 with placebo – will provide 80% power to reject the null hypothesis that aganirsen is no better than placebo. Power computation is based on the chi-square test with a two-sided alpha = 0.05. Assuming that approximately 10% of subjects will not be evaluable due to loss to follow-up and other reasons, a total of 333 subjects are planned for this trial. Missing values of NVG and IOP will be imputed using the last observation carried forward (LOCF) method.

Primary efficacy will be assessed up to four times: two initial futility analyses, followed by an interim analysis for success/futility/continuation and a final analysis. The data will be summarised in tables listing the mean, standard deviation, minimum, median, maximum and number of subjects in a group for continuous data or in tables listing count and percentage for categorical data, where appropriate. Data listing by subject will be provided. The effects of noncompliance, dropouts and covariates, and their interactions with treatment will be assessed to determine the impact on the general applicability of results from this study. Secondary comparisons will be considered exploratory, so that there will be no Type I error adjustment for multiple secondary comparisons.

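### Time to anterior neovascularisation is to be compared by t test or Wilcoxon on the premise of no censored data, but about two thirds of patients are planned to be event-free at week 24

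*Protocol article*

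**What the plan says.** Under Secondary efficacy analysis, the Protocol article states: "Time to development of anterior neovascularisation will be compared by *t* test or Wilcoxon rank sum test (depending on distribution"). The reason given is "since missing data will be imputed using LOCF and there will be no censored data". The same section calls secondary analyses exploratory, and the Statistics section makes no type I error adjustment for them.

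The list of secondary endpoints, placed after the exclusion criteria, has two separate time endpoints. One is introduced by "The secondary endpoints of the trial are the time of development of secondary NVG in the study eye up to week 24"; the other is time to anterior segment neovascularisation (NVI or NVA). The t test/Wilcoxon sentence names only the anterior one.

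On event frequency, the Statistics section says "we estimate that 25% of subjects in the aganirsen group and 48% in the placebo group will develop NVG by 24 weeks", for "200 with aganirsen and 100 with placebo". It also expects about 10% of subjects not to be evaluable, through loss to follow-up and other reasons, and applies LOCF to missing NVG and IOP values. The Discussion notes that NVG takes about 90 days on average to appear but may come much later.

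**The concern.** The choice of test rests on a statement that the plan's own rates contradict. A patient without neovascularisation at week 24, or at the last visit before dropping out, has an event time known only to exceed that visit. LOCF can mark such a patient as still free of neovascularisation at week 24, but it does not say when an event would have occurred.

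The rule is therefore incomplete in the place that matters: a t test or rank test needs one number per patient, and the article does not say which number an event-free patient gets. The candidates behave very differently. One is nearly harmless, one turns dropout into apparent early events, and one discards most of the sample. With the premise left as it stands, the choice could be made after the data are seen.

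**Working it through.** **Inputs.** All come from the Statistics section: event rates 0.25 (aganirsen) and 0.48 (placebo), 200 and 100 evaluable subjects, about 10% not evaluable. Visits every 4 weeks to week 24 are from Table 1.

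**The plan's own figure.** Power at 200:100 and the final two-sided alpha of 0.04288 (z = 2.025) is Φ[(Δ − z·√(p̄(1−p̄)(1/200+1/100))) / √(p₁(1−p₁)/200 + p₂(1−p₂)/100)].
- Neovascularisation: p̄ = 98/300 = 0.327, so Φ[(0.23 − 2.025×0.0574)/0.0586] = 97.4%.
- IOP (0.24 v 0.41): p̄ = 89/300 = 0.297, so Φ[(0.17 − 2.025×0.0559)/0.0577] = 83.7%.
- Both, if independent: 0.974 × 0.837 = 81.5%, in line with the stated 80%. Also 300/0.9 = 333.

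The rates are thus those on which the design stands.

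**Event-free patients.** Events by week 24: 200×0.25 + 100×0.48 = 50 + 48 = 98. Event-free: 300 − 98 = 202, or 67.3% (75% on aganirsen, 52% on placebo). The 25% and 48% count any of NVI, NVA, NVD or NVE, or rescue (Co-primary efficacy I). Anterior neovascularisation is only part of that, so its event-free share should be at least this large.

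**Effect of each convention.** Assumptions, none of them in the article: exponential event times matching the composite rates, events found at the next 4-weekly visit, dropout unrelated to the event. Weekly hazards are −ln(0.75)/24 = 0.0120 and −ln(0.52)/24 = 0.0272, a hazard ratio of 0.44. The no-effect runs use a 33% event rate in both arms. Each setting has 2,000 simulated trials of 200 v 100, tested at two-sided 5%; dropout is given as aganirsen v placebo.

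| Time given to event-free patients | Setting | t test | Wilcoxon | Log-rank |
|---|---|---|---|---|
| Week 24 | effect, no loss | 93% | 95–96% | 98% |
| Week 24 | effect, 10% loss in both arms | 92% | 95% | 97% |
| Week 24 | no effect, 10% loss in both arms | about 5% | about 5% | about 5% |
| Last visit | effect, 10% loss in both arms | 80% | 88% | 97–98% |
| Last visit | no effect, dropout 12% v 6% | 12% | 12% | about 5% |
| Last visit | no effect, dropout 10% v 20% | 24–25% | 24–25% | about 5% |
| Excluded (events only) | effect | 8% | 8% | 97–98% |

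With 222 v 111 (all 333 randomised), the last-visit version has 84% and 90% power, and about 27% type I error at 10% v 20%.

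The 12% v 6% split averages (24 + 6)/300 = 10% overall, so it is compatible with the plan's single figure. The 10% v 20% split averages (20 + 20)/300 = 13.3%.

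The events-only power is low because mean time among patients with an event, 1/λ − 24·S/(1−S), hardly differs between arms: 83.4 − 24×0.75/0.25 = 11.4 weeks against 36.7 − 24×0.52/0.48 = 10.7 weeks.

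**The case against.** The strongest defence is that the sentence implies a value for every patient, most naturally week 24 for those without an event. With complete follow-up that is a common administrative cut-off. The Wilcoxon test with many ties at 24 weeks is then valid and loses only two or three points of power, and even with 10% loss in both arms its error stays near 5%. This stands. But the article does not state that convention, the expected loss breaks complete follow-up, and last-visit time is at least as literal a reading of LOCF. Under the week-24 convention, moreover, the t test compares truncated means.

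Other limits also stand:
- The analysis is exploratory. That excuses the absence of multiplicity adjustment, but it does not make the premise true.
- The 25% and 48% are composite rates. The article gives none for anterior neovascularisation, so the hazard ratio and power figures are illustrations.
- No difference in dropout between arms is stated. Inflated error needs one; equal loss costs only power. A difference is conceivable: patients given anti-VEGF rescue for macular oedema stop study drug, and the Discussion suggests aganirsen may reduce that need. It remains an assumption.

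A reader might infer that the planned test has only about 8% power. That requires dropping two thirds of the patients, which fits poorly with a sentence saying that missing data will be imputed. A reader might also infer that the stated aim of detecting a slowing of NVG is defeated. In the endpoint list that aim belongs to time to secondary NVG, for which the article names no test and may leave it to the full protocol.

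**Conclusion.** The premise of no censored data is wrong on the plan's own rates: about two thirds of patients, and probably more for the anterior endpoint, are right-censored by week 24, and LOCF cannot give them event times. The two-thirds figure needs only the plan's rates and allocation.

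The consequence ranges from small to material according to a convention the article leaves open. Week 24 for everyone costs a few points of power. Last-visit time costs roughly 10 to 18 points with 10% loss in both arms (97–98% down to 88% or 80%), and type I error reaches 12% to 25% under the two assumed unequal dropout patterns. The log-rank test stays near 5% in these runs, where dropout is unrelated to the event; informative dropout would trouble it too.

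This is a should-fix. It would be wrong to infer that the trial's main conclusions are at risk: neither co-primary test, nor the alpha boundaries, nor the sample size uses this analysis.

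**What to change.** In Secondary efficacy analysis, delete the statement that there will be no censored data, and do not use LOCF for event times. Replace the t test/Wilcoxon comparison with Kaplan-Meier curves, a log-rank test and a hazard ratio from a Cox model or, given 4-weekly visits, a discrete-time model with complementary log-log link. Censor event-free patients at their last neovascularisation assessment up to week 24.

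The cost is one paragraph of wording. The visit schedule already collects what is needed, and Trial status says recruitment has not opened.

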**Fig. 1 Fig1:**
[figure not shown]
STRONG trial design

Each patient who has signed the Informed Consent Form is monitored for a period of 30 weeks (24-week treatment phase and 6-week safety follow-up) during which patients will attend nine visits (examination schedule in Table 1; see also Fig. 2. (Additional file 1). A computer-based centralised randomisation scheme for all study sites will employ a 1:1:1 treatment assignment ratio (main study) using block randomisation with sequential numbering for each specific trial site. Subjects, investigators, site personnel, monitoring staff, data management and other sponsor personnel, excluding the Clinical Supplies Unit, will be masked to subjects’ assignments. Only in the case of a serious adverse event (SAE), when the masked information is urgently needed for the treatment of the subject, will treatment allocation be revealed.

**Table 1 Tab1:** Examination schedule

Protocol activity	Screening	Baseline	Week 4	Week 8	Week 12	Week 16 + 20	Week 24/early termination	Week 30 (follow-up)
	V1	V2	V3	V4	V5	V6 + 7	V8	V9
Informed consent	X							
Demographic data (age, gender)	X							
Medical and ophthalmic history	X							
Concomitant medications and procedures	X	X	X	X	X	X	X	X
Adverse events	X	X	X	X	X	X	X	X
NEI-VFQ-25/EQ-5D/ Compliance questionnaires		X			X		X	
Vital signs (blood pressure/pulse)	X				X		X	
Electrocardiogram	X						X	
Haematology	X				X		X	
Blood chemistry	X				X		X	
Urinalysis	X				X		X	
Obtain blood sample for risk factor substudy	X							
Obtain blood sample for biomarker substudy	X				X		X	
Pregnancy test (urine or serum)^a^	X							
Physical exam	X							
Best-corrected visual acuity (BCVA) (ETDRS)	X	X	X	X	X	X	X	X
RAPD	X							
Slit lamp biomicroscopy	X	X	X	X	X	X	X	X
Goldmann perimetry/semi-automatic kinetic perimetry	X^d^							
Schirmer test II (biomarker substudy)	X				X		X	
Goldmann applanation tonometry (±1 h)	X^c^	X	X	X	X	X	X	X^c^
Gonioscopy (study eye only)	X	X	X	X	X	X	X	X
Anterior segment and gonioscopic photography^b^	X		X		X		X	
Posterior segment OCT (SD-OCT)	X		X	X	X	X	X	
Indirect ophthalmoscopy	X	X	X	X	X	X	X	X
Fundus photography^b^	X				X		X	
Fluorescein angiography^b^	X				X		X	
Review inclusion/exclusion criteria	X	X						
Randomisation		X						
Administer study treatment (aganirsen or placebo)		X						
Drug dispensing/return and bottle weight		X	X	X	X	X	X	
Patient diary dispensing/return		X	X	X	X	X	X	
Assess rescue treatment criteria			X	X	X	X	X	X

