**Fig. 2 Fig2:**
[figure not shown]
Standard Protocol Items: Recommendations for Interventional Trials (SPIRIT) figure

The two study groups will be treated with aganirsen ‘low-dose’ (43 μg per day) or ‘high-dose’ (86 μg per day). The control group will receive placebo, as there is no labelled treatment for iCRVO to prevent NVG. The placebo is optically identical to the aganirsen emulsion.

Images of the anterior segment and gonioscopic photos of all patients participating in the STRONG study will be collected and evaluated for neovascularisation within the imaging substudy. Tears and serum samples will be collected during the biomarker substudy from 200 patients to evaluate possible markers for both iCRVO and NVG. The results will be compared with results of healthy subjects already available in a German database. Thirty-three eligible patients will be included in the risk factor substudy across all participating trial sites. At UMC Mainz, 33 age- and gender-matched healthy controls will be recruited. Blood samples will be collected to analyse laboratory parameters for coagulation and fibrinolysis and genetic factors to identify risk factors for iCRVO.

Protocol assistance at the European Medicines Agency (EMA) has taken place to define patients with a high risk for developing NVG. The inclusion criteria must be fulfilled at both the screening and baseline visits.

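### Week-24 BCVA change is adjusted for one baseline reading although two pre-randomisation readings exist; entering both is a nearly free, probably small, gain in precision

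*Protocol article*

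**What the plan says.** All references are to the protocol article; no separate analysis plan is shown.

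- **Endpoint.** The secondary endpoints, listed after the exclusion criteria, include "the development of changes in BCVA (ETDRS letter score) in the study eye up to week 24 (from baseline").
- **Model.** Under *Secondary efficacy analysis*, continuous changes to week 24 "will be assessed by analysis of covariance (ANCOVA), the covariate being a subject"'s "baseline variable, to prevent regression towards the mean". Retinal nonperfusion area is given only as an example. BCVA is not named, but a change in letter score belongs to this class.
- **Measurements.** In Table 1, the row beginning "Best-corrected visual acuity (BCVA) (ETDRS" is marked at screening (V1), at baseline (V2) and at every later visit. Randomisation and first administration are at V2.
- **Eligibility.** *Methods/design* states: "The inclusion criteria must be fulfilled at both the screening and baseline visits". The inclusion criteria set the study eye's letter score below 35.
- **Status.** The same analysis section says that "secondary analyses will be considered exploratory".

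Nothing in the article uses the screening letter score in an efficacy analysis.

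**The concern.** A letter score carries test-retest error, so one reading is an imperfect measure of an eye's acuity before treatment. The ceiling below 35 letters narrows the spread of true acuity among eligible eyes, so error makes up a larger share of what variation remains. A second reading taken before randomisation can improve the prediction of week-24 acuity and so reduce the residual variance of the aganirsen-placebo comparison. The trial collects that reading in every eligible eye and the stated model leaves it out. At stake is some width of the confidence interval for the functional vision outcome, in a rare disease where the article itself expects recruitment to be difficult.

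**Working it through.** **Inputs from the article.** BCVA is measured twice before randomisation. The limit of below 35 letters applies at both readings. The plan states that "a total of 300 evaluable subjects – 200 with aganirsen and 100 with placebo – will provide 80% power"; with 10% not evaluable, 300/0.9 = 333.3, which matches the planned 333. No standard deviation, effect, correlation or power is given for BCVA, so there is no BCVA figure to reproduce.

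**Inputs assumed.** r is the V1-V2 correlation, a the V2-week-24 correlation and b the V1-week-24 correlation. Variances are standardised to 1.

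**Formulas.**
- V2 alone: residual variance = 1 − a².
- V1 and V2 together: residual variance = 1 − (a² + b² − 2abr)/(1 − r²). If a = b = ρ, this becomes 1 − 2ρ²/(1 + r).

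Because V2 is in the model, these values are the same whether the outcome is week-24 acuity or its change from V2.

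**Example.** With r = 0.8, a = 0.5 and b = 0.45, V2 alone gives 1 − 0.25 = 0.750. Both give 1 − (0.25 + 0.2025 − 0.36)/0.36 = 1 − 0.257 = 0.743. The ratio is 0.991, a cut of 0.9%.

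| r | a | b | V2 only | V1 and V2 | Cut |
|---|---|---|---|---|---|
| 0.8 | 0.5 | 0.4 | 0.750 | 0.750 | nil |
| 0.8 | 0.5 | 0.45 | 0.750 | 0.743 | 0.9% |
| 0.9 | 0.5 | 0.5 | 0.750 | 0.737 | 1.8% |
| 0.9 | 0.6 | 0.6 | 0.640 | 0.621 | 3.0% |
| 0.8 | 0.5 | 0.5 | 0.750 | 0.722 | 3.7% |
| 0.9 | 0.7 | 0.7 | 0.510 | 0.484 | 5.1% |
| 0.7 | 0.6 | 0.55 | 0.640 | 0.607 | 5.2% |
| 0.8 | 0.6 | 0.6 | 0.640 | 0.600 | 6.25% |
| 0.8 | 0.7 | 0.7 | 0.510 | 0.456 | 10.7% |

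The gain is nil whenever b = a × r, that is, when V1 adds nothing once V2 is known.

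**Effect of the entry limit.** A simulation drew true acuity from a normal distribution with mean 30 letters and SD 15 or 20. It added measurement error of SD 5 or 8 to each reading and kept eyes with both readings from 0 to below 35. True week-24 acuity was carried forward with coefficient 0.6 or 0.7 plus noise. The restriction lowered the V2-week-24 correlation to between 0.22 and 0.32. The cut from adding V1 was 1.6, 1.8, 1.9 and 2.3% in the four settings.

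**Confidence interval.** Its width scales with the square root of residual variance: √0.98 = 0.990, √0.95 = 0.975, √0.893 = 0.945. Cuts of 2, 5 and 10.7% narrow the interval by about 1.0, 2.5 and 5.5%.

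**Cost.** With 300 evaluable patients, two groups and one covariate, 300 − 3 = 297 degrees of freedom remain; a second covariate leaves 296. The price is of the order of 1/297, or 0.3% of the variance.

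**Both scores, not just their mean.** If change stays measured from V2 and the covariate is replaced by the V1-V2 mean, the residual variance (for a = b = ρ) is 1 − 2ρ²/(1 + r) + (1 − r)/2. At ρ = 0.6 and r = 0.8 this is 0.600 + 0.100 = 0.700, worse than the 0.640 from V2 alone. Entering both scores avoids this.

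**The case against.** The strongest reply is that ANCOVA on a single baseline is a standard, valid analysis that already captures most of the available precision. That stands: there is no bias, no contradiction and no error-rate problem, and the point can only be a refinement.

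Second, the sentence is a general rule for all continuous outcomes, and an unseen analysis plan could define BCVA baseline as the mean of the two visits. This stands in part. One baseline is a sensible common rule: fluorescein angiography and SD-OCT are scheduled at screening but not at V2, so nonperfusion area and retinal thickness have no routine second reading. But the rule as written names one baseline variable, and for BCVA two readings are scheduled.

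Third, a reader might infer a much larger gain. If all three correlations are equal at 0.5 to 0.8, the formula gives a cut of 11 to 20%, equivalent to 12 to 25% more patients. The arithmetic is right, but the design does not support the premise. The occlusion or conversion must be no more than 4 weeks old at both visits, so V1 and V2 lie close together. Week 24 follows about six months of treatment, possible rescue and disease progression. The V1-V2 correlation should therefore exceed the correlation of either with week 24, and there the gain shrinks. That patient-equivalent figure should not be used.

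Nor do the documents show that the interval must be wider than it need be: if V1 adds nothing beyond V2, nothing is lost.

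**Conclusion.** The point holds as a minor improvement confined to BCVA. Two pre-randomisation letter scores exist for every eligible eye and the stated model uses one. Under assumed correlations, adding the other plausibly cuts residual variance by about 1 to 5%. The figure is about 2% with both readings limited to below 35 letters, up to about 11% in favourable cases, and possibly nil. None of these values can be checked against the article, which gives no BCVA standard deviation or correlation. The endpoint is secondary and exploratory with no power target, so the co-primary comparisons, the 300 evaluable patients and the alpha allocation are unaffected.

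**What to change.** Under *Secondary efficacy analysis*, add a clause for BCVA: the ANCOVA includes both the screening (V1) and baseline (V2) ETDRS letter scores as covariates, and change remains defined from V2. The endpoint and the treatment effect being estimated do not change. Leave the single-baseline rule in place for outcomes measured only once before randomisation. Apply the same two covariates, ranked, in the rank-based fallback.

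The cost is one sentence and about one degree of freedom, with no new visit, measurement or patient. The article reports that recruitment has not opened, so the choice can be fixed before any data are seen.
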